###### Acupuncture group

The standard for the acupuncture group is 10 acupuncture treatments, twice a week for 5 weeks of treatment. Using 0.25 x 30 mm sterile needle (Dongbang Medical, South Korea), needle 8 points on the bilateral Taichong (LR3), Sanyinjiao (SP6), Hegu (LI4), and Waiguan (TE5), at a depth of 10 to 25 mm subcutaneously.

###### Electroacupuncture group

The standard treatment regimen for the electroacupuncture group is 10 electroacupuncture treatments, twice a week for 5 weeks.

Using a 0.25 x 30 mm sterilized needle (Dongbang Medical, Korea), needle 8 points on the bilateral Taichong (LR3), Sanyinjiao (SP6), Hegu (LI4), and Waiguan (TE5), at a depth of 10 to 25 mm subcutaneously. The Taichong (LR3) was connected to Sanyinjiao (SP6), and Hegu (LI4) to Waiguan (TE5) with dedicated clips connected to an electro-stimulator (STN-330, Stratech) (red and black color-coded). The frequency of electrical stimulation is set at 2 Hz, the duration of stimulation is 15 minutes, and the intensity is such that the participant is aware of the stimulation but does not feel pain and feels comfortable. After the stimulation, the n eedle is removed and the needle site is sterilized.

###### No-treatment control group

We do not offer acupuncture or electroacupuncture.

- - 1. End of study

After 5 weeks of acupuncture treatment, adverse events and adherence will be assessed, including visual analog scale (VAS), body temperature (thermometer measurement), quality of life assessment questionnaire (WHOQOL-BREF), quality of life assessment (EQ-5D), coldness diagnostic questionnaire, vital signs, weight measurement, laboratory tests, medical history and medication changes, and blinded maintenance survey.

- - 1. Tracking

Four weeks after the end of the study, participants will be evaluated for adverse events, as needed, and checked for changes in visual analog scale (VAS), body temperature (thermometer measurement), quality of life questionnaire (WHOQOL-BREF), quality of life assessment EQ-5D, coldness diagnostic questionnaire, vital signs, weight, medical history, and medication history.

##### Combination Therapy and Cautions

- - 1. In principle, medications and other therapies other than acupuncture should not be administered during the trial period.
    2. You should not take any additional medications during the study period, including below.

Example) Anticoagulants, psychotropic medications, antidepressants, medications related to hyperthyroidism, dietary supplements (such as red ginseng), OTC blood flow enhancers, and other medications that may affect hand and foot colds.

- - 1. However, if necessary, this may be done at the discretion of the investigator based on the following criteria. A participant will be dropped from the study if, in the opinion of the investigator, the medications and therapies administered may affect the endpoints of the study. (See exclusion criteria).

Example) Anticoagulants, psychotropic medications, antidepressants, medications related to hyperthyroidism, dietary supplements (such as red ginseng), OTC blood flow enhancers, and other medications that may affect hand and foot colds.

- - 1. All medications administered and the reason for administration must be documented on the CRF and signed by the investigator.

**Clinical trial flowchart**

| Recruitment and Informed Consent (Visit 0) |
| --- |

↓

| Screening |
| --- |
| Vital signs, height, weight, pathways to and motivation for study participation, demographic and sociodemographic surveys, obstetrical Informational history, medical history and medication history, general physical examination, thermometer measurement, VAS of coldhypersensitivity in the hands and feet, pattern identification questionnaire, laboratory test, Chest X-ray, ECG, Determination of exclusion criteria |

↓

| Randomization |
| --- |
| Acupucnture treatment group, Electroacupuncture treatment group, Control group |

↓

| Baseline (0week) Evaluation (Visit 1) |
| --- |
| Vital signs, weight, medical history and medication history and changes, constitutional diagnostics questionnaire (KS-15), general physical examination, thermometer measurement, VAS of coldhypersensitivity in the hands and feet, quality of life assessment questionnaire (WHOQOL-BREF), quality of life assessment EQ-5D, coldness diagnostic questionnaire, treatment, scheduling next visit |

↓

| Acupuncture or Electroacupuncture treatment (Visit 2~9) |
| --- |
| Acupuncture or electroacupuncture treatment for 5 weeks, vital signs, medical history and medication history and changes, general physical examination, thermometer measurement, VAS of coldhypersensitivity in the hands and feet, checking for adverse events, laboratory tests, scheduling next visit |

| Week 5 Evaluation (Visit 10) |
| --- |
| Vital signs, weight, medical history and medication history and changes, general physical examination, thermometer measurement, VAS of coldhypersensitivity in the hands and feet, quality of life assessment questionnaire (WHOQOL-BREF), quality of life assessment EQ-5D, coldness diagnostic questionnaire, checking for adverse events, laboratory tests, scheduling next visit |

↓

| Daily routine for 4 weeks |
| --- |

↓

| Week 9 Evaluation (Visit 11) |
| --- |
| Vital signs, weight, medical history and medication history and changes, general physical examination, thermometer measurement, VAS of coldhypersensitivity in the hands and feet, quality of life assessment questionnaire (WHOQOL-BREF), quality of life assessment EQ-5D, coldness diagnostic questionnaire, checking for adverse events |

↓

| Data cleaning and statistical processing |
| --- |

↓

#### Observation and inspection items

|  | | Screening | Treatment period | | | |
| --- | --- | --- | --- | --- | --- | --- |
| Visit | | (D -7~0) | Visit 1  (D 1) | Visits 2-9 | Visits 10  (D 35±3) | Visit11  (D 63±3) |
| Obtain written consent | | ● |  |  |  |  |
| Assign a screening number | | ● |  |  |  |  |
| Chest X-ray & EKG^8)^ | | ● |  |  |  |  |
| Inclusion/exclusion criteria^9)^ | | ● |  |  |  |  |
| Randomization | |  | ● |  |  |  |
| No-treatment control group | |  | ■ |  | ■ | ■ |
| Assess treatment adherence | |  |  | ○ | ○ | ○ |
| Whether participants drop out of the study | |  |  | ○ | ○ | ○ |
| Vital signs | | ● | ● | ○ | ● | ● |
| Height, weight, and body mass index (BMI) | | ● |  |  | ●  (Weight only) | ●  (Weight only) |
| Pathways and motivations to participate in  research | | ● |  |  |  |  |
| Demographic, sociodemographic, gynecologic and obstetric information^10)^ | | ● |  |  |  |  |
| Investigate medical and medication  history^11)^ and identify changes | | ● | ● | ○ | ● | ● |
| Constitutional Diagnosis Questionnaire (KS-15) | | ● |  |  |  |  |
| Inspection | |  |  |  |  |  |
|  | General physical exam | ● | ● | ○ | ● | ● |
|  | Thermometer measurement^12)^ | ● | ● | ○ | ● | ● |
|  | VAS of coldhypersensitivity in the hands and feet | ● | ● | ○^13)^ | ● | ● |
|  | Screening for and identifying  adverse events |  |  | ○ | ● | ● |
|  | Pattern identification questionnaire | ● |  |  |  | ● |
|  | Coldness diagnostic questionnaire |  | ● |  | ● | ● |
|  | Quality of life assessment  questionnaire (WHOQOL-BREF) |  | ● |  | ● | ● |
|  | Quality of life assessment EQ-5D |  | ● |  | ● | ● |
| Laboratory test | | ●^14)^ |  |  | ○ |  |
| Acupuncture or electroacupuncture treatment | |  | ○ | ○ | ○ |  |
| Specify next visit date | |  | ● | ○ | ● |  |
| Examiner signature | | ● | ● | ● | ● | ● |

● Conduct all three groups

○ Acupuncture treatment group, electroacupuncture treatment group

■ No-treatment control group

1. Chest x-ray and electrocardiogram performed during screening
2. Performed at screening
3. Age, occupation, digestion, exercise, smoking, drinking, sleep, and motivation to participate
4. Include a medical and medication history related to coldhypersensitivity
5. Bilateral temperature measurements of the anterior thigh (ST32), dorsum of the foot (LR3), palm (PC8) and arm (LU4) at each visit
6. The acupuncture group and the electroacupuncture group additionally VAS of coldhypersensitivity in the hands and feet at Visit 4 and Visit 8
7. Screening includes hematologic tests (WBC, RBC, Hemoglobin, platelet), blood chemistry tests (BUN, creatinine, AST, ALT, r-GTP, glucose), thyroid function tests (free T4, TSH), urine and urinalysis, and pregnancy test (Urine HCG). At D35 (Visit 10), hematology (WBC, RBC, Hg, platelet), blood chemistry (BUN, creatinine, AST, ALT, r-GTP, glucose) will be performed

##### Visit 0 (Screening)

- 1. **Recruiting research participants**

The recruitment of volunteers is conducted through two primary avenues: walk-in patients at the site and open recruitment through outdoor advertising. Volunteers are selected through a competitive recruitment process.

##### Consent and assigning participant identification codes

- - 1. The principal investigator or research associate will fully explain the study to participants in the IRB approved informed consent document and privacy statement.
    2. The research participants are fully explained and given time to think about whether or not to consent to the study, and if they agree, they sign the consent form in their own handwriting with their name and date of consent. The principal investigator or research associate in charge of explaining the consent also writes the date, name, and signature.

※ Note

- The principal investigator or research associate must verify that the signature, name, and date of the participant's consent form match before providing a copy of the consent form.
- If the participant makes a mistake and tries to correct the consent form, the first step is to rewrite it on a new form. Otherwise, write one line in black, followed by a comment, the date of the correction, and your name.

The use of overwrites or modifications is absolutely prohibited.

a. How to make a correction: Draw a line and write "Reason/Correction Date/Signature (or initials)”.

Mislabeling 08-03-24 JBH

146~~/86~~ 88

- Ensure that the date of the consent form is the same as the date of the visit in the medical record, and that the date of the consent form can never be later than the date of the actual assignment of the participant identification code in the clinical trial.
  - 1. Give the consent form and one copy of the consent form to the participant and obtain a handwritten "I have received a copy of the consent form" and the date, name, and signature of the participant.
    2. Assign a participant identification code for screening.

##
[figure not shown]

① S: Screening

② The first two spaces

: When recruiting research participants at Semyung university korean medical hospital at Chungju, capitalize SC for each space.

## S

S C

③ The abbreviations for each sites are as follows

- Semyung university korean medical hospital at Chungju (SC)
- Sangji university korean medical hospital (SJ)
- Dongguk university korean medical hospital at Ilsan (DG)

④ Hyphen followed by three spaces

Number each visit according to the order in which you signed the consent form.

Example) First: 001

Example) The screening number of a participant who signed the 15th informed consent at Semyung university korean medical hospital at Chungju is as follows

[figure not shown]

##### Audience selection

If the person wants to participate in the study, explain the study in detail, have them sign a voluntary written consent form, and give them a screening number.

- - 1. Record vital signs, height, and weight

Vital signs a re assessed at every visit. Vital signs measure blood pressure, pulse rate, and temperature.

- - 1. Demographic and sociographic information

Age, Occupation, Digestion, Exercise, Smoking, Drinking, Alcohol, Sleep

- - 1. Pathways and motivations to participate in research
    2. Gynecology and obstetrics information

Menstrual History

Age at menarche, average menstrual cycle, average menstrual duration, presence or absence of lumps during menstruation, color of menstruation, presence or absence of dysmenorrhea

Leukorrhea

Presence, and color

Pregnancy

Number of past pregnancies, fertility status, lower abdominal coldness

- - 1. Coldhypersensitivity in the hands and feet/other body system medical history and medication history
       - Medical history for coldhypersensitivity in the hands and feet: Conducted at Visit 1

Items related to coldhypersensitivity in the hands and feet (if applicable)

- - - - - Whether or not you've been diagnosed with coldhypersensitivity in the hands and feet
        - Duration of coldhypersensitivity in the hands and feet (months)
        - Previous treatment for coldhypersensitivity in the hands and feet

(medication/ herbal treatment (acupuncture/ moxibustion/ herbal medicine, etc.)/ exercise therapy/ psychotherapy/ other complementary medications)

- - - - - Medications and treatments taking for coldhypersensitivity in the hands and feet
    1. Other organ-specific medical history items- at Visit 1

General physical exam items: at each visit

Obtain a medical history including sensory, musculoskeletal, endocrine, multiple system, urinary, reproductive, digestive, cardiovascular, neurologic, dermatologic, psychiatric, hematologic and lymphatic, and respiratory systems. Any significant findings on examination at the first visit will be recorded in the other body system related fields of the case record sheet, and any significant findings on medical examination that meet the definition of an adverse event after initiation of the study procedure will be recorded on the adverse event case record sheet.

- - 1. Thermometer measurements

In a room at 24±2°C, and 40-60% humidity, expose at least 10cm above both elbows, sit and rest for 10 minutes with lower extremity clothing up to the knee, and take three consecutive measures using a non-contact infrared thermometer at a distance of approximately 3cm from the anterior thigh (ST32), dorsum of the foot (LR3), palm (PC8), and arm (LU4), and record the median value, excluding the highest and lowest values.

- - 1. Hands and Feet Coldness (Visual Analog Scale: VAS)

The VAS of coldhypersensitivity in the hands and feet will be completed by the participants with the assistance of the researcher. On the VAS, participants will mark an “I” for their level of hands and feet coldness.

O, V, not verbalized (to be precise)

[figure not shown]

[figure not shown]
Using a horizontal straight line labeled with numbers from 0 to 10 before the start of the acupuncture treatment and after the end of the treatment, have the participants select the number that corresponds to their level of fatigue. At the left end of the straight line, add the description 'no cold' and at the right end, 'the most severe cold imaginable'. The score is the number they choose.

Only those who have a temperature difference of 0.3℃ or more between the palm (PC8) and arm (LU4) or a temperature difference of 2℃ or more between the anterior thigh (ST32) and dorsum of foot (LR3) measured by a thermometer at the time of the screening visit and a Visual Analogue Scale (VAS) of coldhyepersensitivity in the hands or feet of 4 or more will be enrolled.

- - 1. Pattern identification questionnaire

At Visit 0, the principal investigator or research associate will evaluate participants.

1. The evaluator checks the most appropriate condition for the participants and ◯ marks.
2. The evaluator marks the corresponding pattern identification with a ◯.
   - 1. Constitutional Assessment Questionnaire (KS-15)

Conducted by the principal investigator or research associate at Visit 0

- - 1. Laboratory tests

At visit 0, a 12-lead EKG, chest x-ray, and the following tests are performed

① Hematologic tests: WBC, RBC, Hemoglobin, Platelet;

② Blood biochemistry test: BUN, creatinine, AST, ALT, r-GTP, glucose

③ Urine and urine specimen tests: Blood, Urobilinogen, Bilirubin, Ketone, Protein, Nitrate, Glucose, pH, S.G, LEU, WBC, RBC

④ Pregnancy test (women of childbearing age): Urine HCG;

⑤ Thyroid function tests: free T4, TSH

- - 1. Determining conformance to inclusion/exclusion criteria

At Visit 0, consent, demographic and sociodemographic information, medical history, laboratory tests, pregnancy test and chest x-ray, electrocardiogram, and thermometer measurements to determine if the participant meets the coldhypersensitivity diagnostic criteria will be performed. Results will be combined to make a final determination of eligibility and participants will be contacted by phone within 14 days of testing to schedule Visit 1.

##### B. Visit 1 (D1)

1. Vital signs and weight measurement
2. Verify medical conditions/medications/treatments (check for changes in medical history and medications)

From Screening to Visit 1, investigate whether any new conditions, additional medications, or additional treatments have occurred. If yes, record in the Conditions/Medications/Treatments CRF form.

1. General physical exam

Determine if the patient has any of the conditions listed on the general physical examination form in the CRF at the time of the visit.

If present, circle yes and record in the abnormal findings section below.

V for none.

1. Thermometer measurements

At each visit, before and after treatment, bilateral temperatures at the anterior thigh (ST32) and dorsum of the foot (LR3), and at palm (PC8) and arm (LU4) will be measured using a non-contact infrared thermometer at a distance of, 3cm for three consecutive measurements and the median value excluding the highest and lowest values will be recorded.

1. Hands and feet coldness Visual Analogue Scale (VAS)

The VAS of coldhypersensitivity in the hands and feet will be completed by the participants with the assistance of the researcher. On the VAS, participants will mark an I for their level of hands and feet coldness.

O, V, not verbalized (to be precise)

1. Coldness diagnostic Questionnaire

Let the paticipants fill in the fields that need to be filled in.

The measurement must be performed by a practitioner.

1. The Korean version of the World Health Organization Quality of Life Scale (Short Form) (WHOQOL-BREF) and the EQ-5D Quality of Life Assessment

Check ◯ only for the most appropriate number.

Paper medical records keep the questionnaire and, if the medical record is electronic, the score, description, or item number. or itemized numbers. If this is difficult, create and store a clinical trial-specific paper medical record file.

1. Randomization

Randomize to no treatment, acupuncture treatment, and electroacupuncture treatment.

Record the predetermined randomization table number in the medical record and CRF.

1. Acupuncture or electroacupuncture

An investigator who does not participate in the survey will administer the treatment to the randomized acupuncture group or electroacupuncture group, respectively.

1. Specify your next visit date

In the acupuncture treatment group and the electroacupuncture treatment group, the next visit will be scheduled within 4±3 days after the treatment, based on the principle of twice-weekly treatment. For the no-treatment control group, the next visit will be scheduled on day 35±3 (visit 10) without any treatment.

##### C. Visit 2 ~ Visit 9

1. Participants dropouts

If a participant violates the protocol for any reason, discontinue participation in the study and record it in the End of Study field. If there is no reason for the violation, the clinical trial proceeds.

Withdrawal from a clinical study is based on the following criteria. Participant will be excluded from the study if any of the following conditions apply, as determined by researcher.

a. Participants will be dropped if predicted treatment adherence is less than 70%. Failure to visit within ±3 days of the scheduled visit will be considered a missed visit.

b. Became pregnant during the study

c. If surgery or hospitalization is required due to a disaster such as an accident or the onset of other diseases

d. In case of refusal by a clinical trial participant

e. Prohibited concomitant medications and therapies.

Example) Anticoagulants, psychotropic medications, antidepressants, medications related to hyperthyroidism, dietary supplements (such as red ginseng), OTC blood flow enhancers, and other medications that may affect coldness in the hands and feet.

f. Worsening of coldness in the hands and feet symptoms requiring standard treatment.

f. Serious adverse events that make it unreasonable to continue in the study.

g. Other unavoidable reasons have arisen that make it impossible to continue the study or that the principal investigator believes would have affected the results of the study.

1. Measure vital signs

Measure and record vital signs.

For vital signs, check and record body temperature, systolic blood pressure, diastolic blood pressure, and pulse rate.

1. Verify medical conditions/medications/treatments (check for changes in medical history and medications)

Check for any new medical conditions, additional medications, or other treatments during Visits 2 through 9.

If so, record it in the Condition/Medical Supplies/Treatment CRF form.

1. General physical exam

Determine if the participant has any of the conditions listed on the general physical examination form in the CRF at the time of the visit.

If present, circle yes and record in the abnormal findings section below.

V for none.

1. Acupuncture or electroacupuncture

A researcher who did not participate in the survey will administer the appropriate treatment to the randomized acupuncture or electroacupuncture arm.

1. Thermometer measurements

At each visit, before and after treatment, bilateral temperatures at the anterior thigh (ST32) and dorsum of the foot (LR3), and at the palm (PC8) and arm (LU4) will be measured using a non-contact infrared thermometer at a distance of 3 cm for three consecutive readings, and the median value excluding the highest and lowest readings will be recorded.

1. Visual Analogue Scale (VAS) of coldhypersensitivity in the hands and feet

The VAS of coldhypersensitivity in the hands and feet will be completed by the participant with the assistance of the researcher. On the VAS, participants will mark an I for their level of hands and feet coldness.

O, V, not verbalized (to be precise)

1. Screening for and identifying adverse events

Check for any adverse events that occurred during the acupuncture treatment.

If there are any adverse events, complete an adverse event report in the CRF.

Adverse event reporting procedures are in accordance with the adverse event reporting SOP and the standard operating procedures for acupuncture treatment administration.

1. Specify your next visit date

Notify the study box of the date of the next visit, which should be within 4±3 days from the previous visit, based on the principle of twice-weekly treatments.

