The significance level (α), the probabiiity of committing a TypeⅠerror, was set at 0.05, and the probability of committing a TypeⅡerror (β) was assumed to be 0.2. The number of participants in the electroacupuncture treatment group and the no-treatment control group was set to be the same, and the formula for estimating the number of participants by comparing the mean of the two groups was as follows.

[figure not shown]

N = [2*(1.96+0.84)^2*1.17^2]/(1.04)^2=17.625 ≒ 18

Based on the above, the number of participants is 18 in each arm. Considering a 25% dropout rate, 24 participants will be enrolled per arm.

18 ÷ (1-0.25) =24

Therefore, we plan to enroll 24 participants in each of the acupuncture treatment group, electroacupuncture treatment group, and no-treatment control group for a total of 72 participants to be analysed.

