#### Test Methods

##### Test design

This study is a randomized, multicenter, parallel design, clinical trial. After receiving sufficient explanation from the researchers involved in this study and voluntarily signing the consent form, participants who are deemed suitable for the study by reviewing the inclusion and exclusion criteria according to the protocol will be assigned a patient identification code. Blood tests will be performed, and they will be randomized to the acupuncture treatment group, electroacupuncture treatment group, and no-treatment control group at a later screening visit.

Each participant will have a screening visit, followed by randomization. If assigned to the acupuncture arm or the electroacupuncture arm, participants will attend bi-weekly visit for a total of 5 weeks, resulting in 10 visits for acupuncture or electroacupuncture, respectively. Subsequently, a follow-up assessment will be conducted 4 weeks later. The control group is required to attend three visits, designated as Visit 1, Visit 10, and Visit 11, respectively.

[figure not shown]

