##### Randomization Methods and Blinding

- - 1. Overview

After the particioants have signed the informed consent form, they will be randomized to the acupuncture treatment group, the electroacupuncture treatment group, or the no-treatment control group at Visit 1, if they are deemed eligible for the study after reviewing the inclusion and exclusion criteria. Participants will be instructed on the procedures and visit dates, and will receive 10 treatments twice a week for 5 weeks (±3 days) according to the study schedule. All three arms will be assessed for efficacy 5 weeks (±3 days) after randomization and followed up at 9 weeks (±3 days).

- - 1. Randomization and stratification methods

Patients who agree to participate in this study will be assigned a screening number in the order of their written consent, and if more than one person is screened on a single day, the screening numbers will be assigned in the order of their consent. Randomization codes will be provided by an independent statistician or a third independent investigator with a 1:1:1 ratio of acupuncture, electroacupuncture, and no-treatment control groups. Randomization numbers will be generated using the blockrand package in R 3.4.2 or later, stratified by site at randomization, and block randomization will be used to ensure that the number of participants in each arm is approximately equal. At each site, participants will be assigned numbers based on the order of screening completion.

- - 1. Assignments

This study will use the sealed envelope method. The independent statistician or third independent investigator who generated the randomization code will place a piece of paper with the randomization code inside the opaque envelope, seal it, and give it to the authorized representative at each site. If a participant who has given written consent passes the screening assessment, the authorized representative will open the envelope in the order in which the screening assessment is completed, verify and record the participant's randomization code and assignment arm.

- - 1. Blindfold

This study is an open-label trial in which all arm assignments are not blinded to outcomes. However, we will blind the assessors who evaluate participants' symptoms separately from the treating physician to minimize possible bias in the assessment.

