##### F. End of Study

1. V for Yes if the trial is finalized and record the end date.

Example) Was the trial completed in accordance with the protocol?

□ Yes → End date 20□□Year □□Month □□Day

1. If you dropped out of the study midway through or lost compliance, V-Check No in the CRF form [Study Terminated], complete the date of the dropout or withdrawal, and V-Check the reason for the dropout or withdrawal.

Example) □ No → Suspension or dropout date20□□Year □□Month □□Day

Causes of study discontinuation or dropout

- - Violation of Inclusion/Exclusion Criteria
  - Unidentified systemic disease before clinical trial
  - Adverse reaction
  - Intercurrent illness (not intervention related)
  - Participant's request for withdrawal (other than adverse reaction)
  - Investigator indicated termination
  - Exclusion from study due to non-adherence to protocol
  - Pursuit failure
  - Other other ( )

1. Make any notes in the progress or overall comments.
2. The principal investigator must sign and date the CRF after finalizing it.

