##### Worsening of coldhypersensitivity in the hands or feet requiring standard treatment.

##### Serious adverse events that make it unreasonable to continue in the study.

##### Other unavoidable reasons have arisen that make it impossible to continue the study or that the principal investigator believes would have affected the outcome of the study.

For those who drop out, we will recommend conventional medical treatment of coldhypersensitivity in the hands and feet if the participant wants additional treatment, or standardized treatment if the participant wants maintenance treatment. The duration of treatment for these dropped particiapnts and the issue of compensation with or without treatment will be determined by the institutional review board according to the condition of the dropped participants and the causal relationship with acupuncture treatment.

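### Drop rules take randomised participants out of the study rather than only off treatment, so the main ITT analysis must fill some Week 5 VAS values by LOCF, which works differently by arm

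*Protocol*

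**What the plan says.** The dropout item under Visit 2 ~ Visit 9 opens: "Participant will be excluded from the study if any of the following conditions apply, as determined by researcher". Its grounds are predicted adherence below 70%, pregnancy, surgery or hospitalisation, refusal, prohibited medication or therapy, worsening that needs standard treatment, serious adverse events, and a residual item: "Other unavoidable reasons have arisen that make it impossible to continue the study or that the principal investigator believes would have affected the results". The section on study discontinuation and exclusion repeats the list and ends with a reason "that the principal investigator believes would have affected the outcome of the study". Combination Therapy and Cautions adds: "A participant will be dropped from the study if, in the opinion of the investigator, the medications and therapies administered may affect the endpoints".

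For a dropped participant, End of Study asks the investigator to "complete the date of the dropout or withdrawal, and V-Check the reason for the dropout or withdrawal". The discontinuation section offers dropouts treatment advice. Neither asks for a VAS.

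Statistical Methods, General principles, defines ITT as all eligible, consenting, randomised participants whatever violations or dropouts occur. The primary endpoint section makes ITT the main analysis set. Missing efficacy values are filled by LOCF (General principles; Analyzing missing values).

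The arms differ in what can be carried. Test design states: "The control group is required to attend three visits, designated as Visit 1, Visit 10, and Visit 11, respectively". The footnote to the visit schedule gives the two needled groups additional VAS measurements at Visits 4 and 8.

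**The concern.** The plan promises an ITT analysis but stops collecting the data it needs. Stopping treatment and leaving follow-up are treated as one event, although most of the listed grounds are reasons to stop needling and do not prevent a participant from marking a VAS at Week 5.

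The gap is then filled by a rule that is not neutral between arms. A control without a Week 5 value receives a change of exactly zero. A needled participant may receive a change that already holds part or all of the treatment effect, or zero if dropped before Visit 4. The main comparison can therefore move in either direction, even if dropping out is unrelated to response. An SAP can replace LOCF with another method, but it cannot recover a VAS that was never collected.

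**Working it through.** **Inputs from the protocol (Number of participants; General principles).** Mean changes in the reference trial: -1.52 and -0.48, difference 1.04. Pooled SD 1.102. Two-sided alpha 0.05, beta 0.2. "Considering a 25% dropout rate, 24 participants will be enrolled per arm"

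**The plan's own figure.** 2 × (1.96 + 0.84)² × 1.102² / 1.04² = 17.61, so 18 per arm, and 18 / 0.75 = 24. This agrees with the stated 18 and 24. (The printed formula shows 1.17, which would give 19.84. That is a separate matter, and 1.102 is used here.)

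**Benchmarks, exact t-test, SD 1.102, difference 1.04.** 24 per arm with complete data: power 89.3%. 18 per arm: 78.5%.

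**Assumptions.** k of 24 are dropped in each arm before Visit 10, unrelated to response. No-treatment controls change by -0.48 (the placebo value of the reference trial). Those dropped would otherwise have changed like the rest. Shifts are measured against the difference that observed Week 5 values would give.

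**Case A: no true effect, and needled dropouts carry a Visit 8 value equal to their Week 5 mean.** Needled mean: -0.48. Control mean: (1 - k/24) × (-0.48). The shift is k/24 × 0.48 towards needling.

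**Case B: true difference 1.04, and needled dropouts carry Visit 1.** Both arm means shrink by the factor 1 - k/24. The shift is k/24 × 1.04 against needling.

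Error and power come from simulation: 60,000 trials per setting, two-sample t-test.

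| k of 24 per arm | A: shift towards needling | A: two-sided error | B: shift against needling | B: power |
|---|---|---|---|---|
| 2 | 0.04 | 5.2% | 0.09 | 85% |
| 4 | 0.08 | about 5.5% | 0.17 | 79% |
| 6 (planned 25%) | 0.12 | 6.7% | 0.26 | 72% |

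**Between the cases, k = 6, true difference 1.04.** Let needled dropouts carry a fraction f of -1.52. The needled mean moves towards zero by 0.25 × 1.52 × (1 - f) = 0.38 × (1 - f), and the control mean by 0.25 × 0.48 = 0.12.
- f = 0: difference 1.04 - 0.38 + 0.12 = 0.78.
- f = 0.5: 1.04 - 0.19 + 0.12 = 0.97.
- f = 1: 1.04 + 0.12 = 1.16.

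The two movements cancel at f = 1 - 0.12/0.38 = 0.68. The sign therefore depends on when needled participants are dropped, which cannot be known in advance.

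**Sensitivity to the control change.** If untreated controls do not change at all, the shift in case A is 0. With a true difference of 1.04, case B stays at 0.25 × 1.04 = 0.26 for k = 6.

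**The residual ground alone.** Assume 2 of 24 dropped from one needled arm, a drop decision that correlates 0.3 with the Visit 8 change, and a Visit 8 to Week 5 correlation of 0.5 to 0.7. The simulated ITT bias is 0.012 to 0.025 against needling, with power 87.7% to 88.4%. The supplementary PP bias is 0.025 to 0.039 towards needling, with error 5.0% to 5.2%.

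**The case against.** **Not every drop loses Week 5.** The Visit 10 section lists the dropout check first and then every assessment, VAS included. The discontinuation section judges adherence at the end of the study, and the schedule places dropout checks at Visits 10 and 11 as well. People dropped then may already have a Week 5 value. This stands, so the point is limited to drops before Visit 10, which the Visit 2 ~ Visit 9 section allows.

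**The protocol says all three arms are assessed at 5 weeks, and its analysis-set wording implies that some violators have final data.** Both are true. But the first is a general schedule statement, and neither says that an excluded participant returns.

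**Some data would be missing anyway.** Refusals and losses to follow-up cannot be recovered by wording. The schedule marks the dropout check for the needled arms only, so a control missing at Week 5 is more likely to be a refusal or no-show. This also stands. The k = 6 row is an upper bound on what the rule could cost, not an estimate of what the fix recovers.

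**A reader might infer that the residual ground lets the investigator remove poor responders.** The protocol does say: "This study is an open-label trial in which all arm assignments are not blinded to outcomes". The documents do not support the inference. An unavoidable reason must first have arisen, and drugs, worsening, serious adverse events and refusal have their own grounds. Symptom assessors are blinded and separate from treatment, and nothing shows that interim VAS would be seen before a decision. Even mild selective use moves the main result by no more than about 0.03, in the conservative direction.

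**Conclusion.** The point holds for participants dropped before Visit 10: the protocol ends their participation, schedules no Week 5 VAS, and then relies on LOCF in its main analysis. Because carried values differ by arm, the result can be distorted without any selective dropping.

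At the planned 25% dropout, the bound is 0.12 towards needling (error 6.7%) or 0.26 against (power 72% instead of 89%), on an expected difference of 1.04. These figures assume that the reference trial's placebo change applies to untreated controls, that all 6 of 24 per arm are dropped before Visit 10, and that dropping is unrelated to response. The protocol does not split the 25% by ground, so the avoidable share is unknown and below the bound. The residual ground is a minor contributor. This is a worthwhile, low-cost correction and does not show that the main result would be wrong.

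**What to change.** In Combination Therapy and Cautions, the dropout item under Visit 2 ~ Visit 9, and the discontinuation section, make every ground other than withdrawal of consent a reason to stop study treatment only. State that Visit 10 and Visit 11 outcomes are collected from all randomised participants in all three arms unless consent is withdrawn, and that ITT uses the observed values. PP may still leave these participants out. Deleting the limb about what the principal investigator believes affected the results or outcome is an optional tidy-up.

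The cost is wording changes and, at most, 18 planned dropouts × 2 visits = 36 visits that are already scheduled. Stopping for safety or at the participant's request is unaffected. Some Week 5 values will reflect other therapy taken after stopping, which is consistent with an ITT set defined whatever violations or dropouts occur.
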